## Abstract

**Background:**

Epiretinal membrane (ERM) causes visual impairment such as reduction in visual acuity and metamorphopsia due to retinal traction. With the improvement of optical coherence tomography (OCT) and microincision vitrectomy surgery (MIVS), the surgery of ERM has significantly advanced. However, there have been no large-scale studies on the following: (1) how to evaluate visual impairment in ERM, (2) the relationship between OCT findings and visual function, (3) when is the optimal timing of surgery, and (4) the relationship between the surgical instruments as well as techniques and prognosis. The purpose of this study was to obtain evidence regarding these ERM surgeries.

**Methods and design:**

This is a prospective, multicenter cohort study of ERM surgery in Japan from March 1, 2023, to March 31, 2027 (UMIN000048472, R-3468-2). Patients who underwent ERM surgery during the study period and agreed to participate in this study will be included. The goal is to have a total of 5,000 eyes surgically treated for ERM. The following data will be collected: age, gender, medical history, subjective symptoms, visual function before and 6 and 12 months after surgery, clinical findings, OCT data, surgical technique, instruments used in surgery, and complications.

**Discussion:**

The results of this study will support the surgical decisions and procedures in ERM practices.

## Introduction

Epiretinal membrane (ERM) is a common type of fibrocellular proliferation found on the internal limiting membrane (ILM) of the retina, and is significantly associated with aging [1–3]. The major symptoms of ERM include reduced visual acuity, metamorphopsia, and aniseikonia [4–8].

Recently, considerable improvements have been observed in optical coherence tomography (OCT) and micro incision vitrectomy surgery (MIVS) system, and ERM surgery is more advanced than ever before. However, there are still many unsolved issues involving ERM surgery, such as evaluation protocols regarding visual impairment, the relationship between OCT findings and visual function, the optimal timing of surgery, and the relationship between ERM surgical techniques as well as the instruments and prognosis, and lastly, the safety of the surgery. Although reports on each of these topics have been published from a single center or a small number of centers, no generalizable conclusions have been arrived at.

Randomized controlled trials (RCTs) are the best way to obtain high levels of evidence for treatment efficacy. However, it is difficult to conduct an RCT for a disease for which existing treatments have already been established, such as surgery. Recently, real-world data analysis with a quasi-experimental design using big data derived from day-to-day clinical practice has been conducted instead of RCTs. A report on reoperation after ERM surgery based on IRIS (Intelligent Research In Sight) registry data has been published in the United States [9]. In Japan, the Japanese Retina and Vitreous Society (JRVS) conducted a nation-wide rhegmatogenous retinal detachment (RRD) registry study and reported the prognosis of RRD surgery using big data [10–22].

In this study, with ERM as the target disease, we represent JRVS aiming to obtain a high level of evidence regarding the surgery for ERM based on a nation-wide registry, including visual function tests in ERM and the optimum timing of surgical intervention along with the OCT findings, and the relationship between surgical technique and pre- and postoperative visual functions.

## Methods

### Study design and ethical considerations

This is a prospective, multicenter cohort study of ERM surgery in Japan from March 1, 2023, to March 31, 2027. This study adheres to the Declaration of Helsinki and was approved by the Ethics Committee of Kyoto University (UMIN000048472, R-3468-2). In this study, the need to obtain written informed consent from the patients will be waived off as no randomization will be included. This study will be carried out using the opt-out approach following the Ethical Guidelines for Medical and Biological Research Involving Human Subjects.

### The sample size, inclusion, and exclusion criteria

The goal is to register a total of 5,000 eyes surgically treated for ERM. The following patients will be included in the study: (1) who undergo ERM surgery and (2) who can be followed up for 1 year after surgery, regardless of whether the ERM is idiopathic or secondary.

### Registered data

The following data will be collected: age, gender, medical history, subjective symptoms, visual function, clinical findings, OCT data, surgical technique, instruments used in surgery, and complications (Table 1). Snellen visual acuity will be measured before and 6 and 12 months after surgery and decimal best corrected visual acuity will be converted to logMAR units for analysis. The collected data will be stored securely in locked computers at each facility, anonymized, and registered via the Internet. The data center will be placed in the JRVS office, and the data will be stored and managed under utmost security. All data will be checked at least twice by two researchers. When inconsistencies or outliers are found, the committee will contact the facility to confirm them, and if they cannot be confirmed, a final decision will be made by the committee.

**Table 1 pone.0297347.t001:** The list of collected information of the J-ERM registry.

Preoperative characteristics	Surgical procedure	Postoperative characteristics
		(6 months/12 months postoperatively)
Age	Date of surgery	Best-corrected visual acuity
Sex	Combined cataract surgery	M-CHARTS score
Laterality	Gauge of vitrectomy instruments (23/25/27)	Contrast sensitivity
Symptoms	Adjuvants	CRT
Best-corrected visual acuity	Presence of PVD	Postoperative complications
Spherical equivalent	Forceps	
Intraocular pressure	Macular procedures performed during ERM peeling	
Axial length	Handling of EP	
M-CHARTS score	Macular staining	
Contrast sensitivity	Intraocular tamponade materials	
Lens status	Intraoperative complications	
Complication of posterior capsule opacification		
Complication of glaucoma		
Primary or secondary ERM		
Classification of ERM		
(ERM/MPH/LMH/FS)		
High myopia		
Cause of secondary ERM		
ERM of the fellow eye		
OCT device		
CRT		
ERM staging^a^		
Presence of PVD		
Complication of VMT		
Presence of EIFL		
Presence of cystoid macular edema		
Presence of ellipsoid zone disruption		
Presence of acquired vitelliform lesion		

Abbreviations: ERM, epiretinal membrane; PVD, posterior vitreous detachment; VMT, vitreomacular traction; TA, triamcinolone acetonide; EP, epiretinal proliferation; MPH, macular pseudohole; LMH, lamellar macular hole; FS, foveoschisis; OCT, optical coherence tomography; CRT, central retinal thickness.

^a^Govetto et al. AJO 2017

### Safety

Since this is an observational study, there are no risks associated with participation in this study that are more than the standard care for the treatment of ERM practice in Japan.

### Statistical analysis

An overview of the clinical picture and what treatment options are selected will be evaluated by descriptive statistics. Postoperative visual function and complications will also be examined by multivariate analysis to determine the relevant pre- and intraoperative factors. Continuous variables will be analyzed with the Mann-Whitney U test or the Kruskal-Wallis test (or with the Student’s *t-test* or one-way ANOVA for parametric tests), and categorical variables will be analyzed with the chi-squared test or Fisher’s exact test. A *P* value of < 0.05 will be considered statistically significant. Multivariate analysis will be conducted considering potential confounding findings with covariates associated with both the selection of treatment options and the outcome. In addition, statistical methods such as multilevel mixed models and quasi-comparative study designs with propensity scores and control variables will be used.

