The following four points are debatable and/or unknown intraoperatively and postoperatively in ERM surgery: i) whether or not ILM peeling should be performed, ii) the choice of surgical adjuvants for staining, surgical instruments (the gauge size in vitrectomy system and type of forceps), intraocular tamponade material selection; iii) the choice of how to handle EP in cases with EP; iv) the incidence of postoperative complications and factors involved in their occurrence. While ILM peeling can reduce the recurrence of ERM [42–44], ILM peeling is known to decrease retinal sensitivity [25, 45, 46]. No conclusion has been reached as to which cases should be treated with ILM peeling. Moreover, brilliant blue G, and indocyanine green, and triamcinolone acetonide are commonly used as visualization agents for membrane peeling [47–49], but they are used at the discretion of each physician, and no clear criteria exist for their use. Similarly, because no large-scale studies have been conducted, the choice of the gauge size of the vitrectomy system, the type of intraocular forceps, and the use of tamponade material (balanced salt solution, air [50, 51], and gas [52]) is at the discretion of each surgeon. In addition, various techniques have been reported for ERM cases associated with EPs, which are frequently seen in LMH, including EP removal [53, 54], EP embedding [55, 56], and ILM peeling without EP implantation [57]. However, there have been no large-scale studies on the postoperative outcomes of these techniques. Furthermore, postoperative complications of ERM include cataract progression [58], posterior capsular opacification [59, 60], epiretinal membrane recurrence [44], cystoid macular edema (CME) development [61], postoperative endophthalmitis [62, 63], retinal tears and detachment [64], and macular hole [65]. However, the incidence of each of these complications is low, and no analysis of large case series has been performed since the widespread use of MIVS, so the exact incidence and pre- and intraoperative factors associated with each complication are unknown. To address these important questions, we will employ statistical techniques like multivariate analysis and other modeling approaches, such as multilevel mixed models. In addition, statistical methods such as multilevel mixed models and quasi-comparative study designs with propensity scores and control variables will be used.

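### Student's t-test and one-way ANOVA are named as the parametric options although surgeon-chosen groups may differ in size and spread; the Welch forms would keep unadjusted P values near their nominal level

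*Protocol article*

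**What the plan says.** The Statistical analysis section of the protocol article puts rank tests first: "Continuous variables will be analyzed with the Mann-Whitney U test or the Kruskal-Wallis test". The parenthesis that follows offers Student's t-test or "one-way ANOVA for parametric tests". No unequal-variance form is named. One significance rule covers everything: a P "value of < 0.05 will be considered statistically significant". It is not restricted to the adjusted analyses.

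The same section plans more than these tests. Postoperative visual function and complications are to be examined by multivariate analysis, adjusting for "covariates associated with both the selection of treatment options and the outcome". It adds that "multilevel mixed models and quasi-comparative study designs with propensity scores and control variables will be used". The Discussion assigns the open questions on surgical technique to the same family of methods.

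On how groups arise, the Discussion says that the choice of gauge, forceps and tamponade "is at the discretion of each surgeon". The target is 5,000 eyes. Expected group shares and standard deviations are not given.

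**The concern.** Student's t-test and classical one-way ANOVA pool the variance across groups. With equal group sizes the two-group test tolerates unequal variances well. With unequal sizes the pooled variance is dominated by the larger group, so the standard error of the difference is wrong whenever the spreads differ. If the smaller group is the more variable, the standard error is too small and P is too small. If it is the less variable, P is too large.

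Nothing in this design balances the groups. Technique is the surgeon's choice, idiopathic and secondary ERM are both enrolled, and the handling of epiretinal proliferation concerns only the eyes that have it. Case mix, and with it the spread of outcomes, may therefore differ by technique. What is at stake is whether an unadjusted P below 0.05 for an uncommon technique carries the error rate that the plan attaches to it.

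**Working it through.** **The plan's own figure.** The only figure affected is the 0.05 level. The plan states no calculation, so there is nothing to reproduce. The check asks what error rate Student's t actually has when it is run at 0.05.

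**Inputs from the article.** Significance level 0.05 (taken as two-sided, since sidedness is not stated); total N = 5,000 eyes.

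**Inputs assumed, not in the article.** The share of eyes in the smaller group (5%, 10% or 50%), and the ratio r of its SD to that of the larger group (0.7 to 2.0). The larger group's SD is set to 1.

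**Formulas (large sample, no true difference in means).**

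- True variance of the difference: V_true = r²/n1 + 1/n2
- Variance used by Student's t: V_pooled = [(n1·r² + n2)/N] × (1/n1 + 1/n2)
- True type I error = 2 × [1 − Φ(1.96 × √(V_pooled/V_true))]

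**Example 1: 10% share, r = 1.3 (n1 = 500, n2 = 4,500).**

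- V_true = 1.69/500 + 1/4,500 = 0.003602
- V_pooled = (845 + 4,500)/5,000 × 0.002222 = 1.069 × 0.002222 = 0.002376
- √(0.002376/0.003602) = 0.812; 1.96 × 0.812 = 1.592
- True type I error = 0.111

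**Example 2: 10% share, r = 0.7.**

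- V_true = 0.49/500 + 1/4,500 = 0.001202
- V_pooled = (245 + 4,500)/5,000 × 0.002222 = 0.949 × 0.002222 = 0.002109
- √(0.002109/0.001202) = 1.324; 1.96 × 1.324 = 2.596
- True type I error = 0.009

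**Results at nominal 0.05.**

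| Smaller group's share | r = 0.7 | r = 1 | r = 1.3 | r = 1.5 | r = 2.0 |
|---|---|---|---|---|---|
| 5% | 0.007 | 0.050 | 0.121 | 0.172 | 0.284 |
| 10% | 0.009 | 0.050 | 0.111 | 0.154 | 0.245 |
| 50% | 0.050 | 0.050 | 0.050 | 0.050 | 0.050 |

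Only the share and r matter, because N cancels from V_pooled/V_true. A larger registry with the same proportions would have the same error rate.

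**Simulation check of Student's t (normal data, N = 5,000, 4,000 runs).**

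| Share, r | Simulated | Formula |
|---|---|---|
| 10%, 1.5 | 0.140 | 0.154 |
| 10%, 2.0 | 0.236 | 0.245 |
| 5%, 1.5 | 0.173 | 0.172 |
| 20%, 1.5 | 0.130 | 0.121 |

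The differences go in both directions and do not alter the picture. Across all simulated scenarios Welch's t stayed between 0.044 and 0.055.

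**One-way ANOVA (3,000 runs, assumed groups of 250, 3,750 and 1,000).** The error was 0.136 when the smallest group's SD was 1.5 times that of the others, 0.228 at 2 times, and 0.022 at 0.67 times. Classical ANOVA thus behaves in the same way.

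**Mann-Whitney, the test listed first (1,500 runs, 10% share).** The error was 0.095 at r = 1.5, 0.119 at r = 2 and 0.012 at r = 0.5. The rank test is also affected by unequal spread, though less than Student's t.

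**The case against.** The strongest objection is that the technique questions do not rest on these tests. Both the Statistical analysis section and the Discussion direct them to multivariate, mixed-model and propensity analyses, and the parametric tests are a parenthetical alternative to rank tests. This stands, and it limits the weight of the point. It does not remove it, because the 0.05 rule also covers the unadjusted comparisons.

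A second objection is that the size of the effect comes wholly from assumed shares and SD ratios. This also stands. Surgeon discretion makes imbalance plausible but does not establish a 5% or 10% group, and the article does not say that uncommon techniques go to more variable eyes. A reader might infer that the reported P values will be several times too small. The documents do not support that: the direction is unknown, a ratio of 1.3 gives little more than a doubling of the error rate, and a ratio below 1 makes the test conservative.

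A third objection is that the choice between Student and Welch, and the rule for choosing rank or parametric tests, usually belong in an analysis plan that is not shown. For the choice rule this is right, and its absence is not held against the article. A reader might also infer that analysts could run both tests and keep the smaller P. The text does not say so; its natural meaning is a choice by type of distribution. The equal-variance tests, however, are stated methods and not an omission, so naming better ones is fair comment.

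**Conclusion.** The point holds as a modest improvement to a stated method. Student's t and classical one-way ANOVA do not hold the 5% level when group sizes and spreads both differ, and the registry's size gives no protection. If a technique is used in 5 to 10% of eyes, the true type I error of Student's t ranges from below 1% (SD ratio 0.7) through 11 to 12% (ratio 1.3) to 25 to 28% (ratio 2.0). These figures are conditional on shares and SD ratios that the article does not give. The article does not show that P values will be wrong in a particular direction, nor that the technique conclusions depend on these tests.

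**What to change.** In the Statistical analysis section, name Welch's t-test and Welch's ANOVA as the parametric options in place of Student's t-test and classical one-way ANOVA. State that unadjusted group comparisons are descriptive and that conclusions on technique come from the adjusted models already planned. Use robust standard errors in those models where spread differs between groups, because a standard mixed model also assumes constant residual variance. Where rank tests are kept, note that they too are sensitive to unequal spread.

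The cost is a few sentences of wording. Data collection and sample size do not change, and there is no practical loss of power with 5,000 eyes.

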## Discussion

With improvements in the performance of diagnostic equipment and surgical instruments, ERM has become the leading macular disease for which vitrectomy is performed. However, there is no clear evidence as to which cases should be operated on or as to the efficacy and safety of surgery. Although there have been many retrospective studies on ERM, they have been conducted in a small number of facilities with a small number of cases, and the studies on ERM surgery have had short postoperative follow-up periods [23–25]. The present study is a large, multicenter, prospective, observational study in Japan, with a planned follow-up period of up to 1 year after surgery. The design of this study overcomes the shortcomings of previous studies and has the potential to establish evidence regarding ERM surgery.

Regarding the evaluation of visual impairment and the prognosis of visual function in ERM, there are many unanswered questions. Visual impairment in ERM has traditionally been assessed by visual acuity testing [23, 24]. However, even patients with good visual acuity may show metamorphopsia [5, 26] and reduced contrast sensitivity [27], and these tests are useful in the evaluation of visual function from multiple viewpoints before and after surgery in ERM. In this study, we will evaluate metamorphopsia and contrast sensitivity as well as analyze the course of each parameter both pre- and post-surgery. We also plan to collect data on the condition of the lens [27, 28] and the presence of posterior vitreous detachment (PVD) [29], which may affect various visual function tests. In addition, identifying the extent to which surgical intervention is performed for ERM at the time of visual deterioration and the factors associated with postoperative visual function may provide insight into the appropriate timing of surgical intervention. Specifically, as various OCT data, including B-scan and 3D images, will be collected from all patients in this study, we will analyze the relationships between postoperative visual functions and the staging of B-scan images [30] and the maximum depth of the retinal folds [31], thereby determining the appropriate timing of surgery.

While the morphological analysis of ERM has progressed with the development of OCT, detailed classification of ERM based on OCT findings has raised new clinical questions regarding the relationship between various OCT findings and visual function in ERM. OCT findings in ERM include ectopic inner foveal layer (EIFL) [30], macular cysts [32], EZ disruptions [33], and central foveal bouquet abnormalities [33] on B-scan images, and retinal folds on en face images [31, 34–38] constructed from 3D retinal images. Although the relationship between these findings and various visual functions and their application to the criteria for surgery have been reported [31], all of these studies were conducted in a small number of patients. On the other hand, epiretinal proliferation (EP) has recently been distinguished as a distinct lesion with OCT findings similar to those of ERM but with completely different characteristics, such as traction and histological findings [39, 40]. Based on this finding, Hubschman et al. proposed an OCT-based consensus definition of lamellar macular hole (LMH) and related diseases, classifying them into three categories: LMH, which is frequently associated with EP; ERM-Foveoschisis (FS), which traction by ERM is the primary pathology; and macular pseudohole (MPH) [41]. This study may provide insight into the postoperative prognosis of ERM, LMH, and related diseases and may lead to the discovery of OCT findings that predict postoperative visual outcomes.

The following four points are debatable and/or unknown intraoperatively and postoperatively in ERM surgery: i) whether or not ILM peeling should be performed, ii) the choice of surgical adjuvants for staining, surgical instruments (the gauge size in vitrectomy system and type of forceps), intraocular tamponade material selection; iii) the choice of how to handle EP in cases with EP; iv) the incidence of postoperative complications and factors involved in their occurrence. While ILM peeling can reduce the recurrence of ERM [42–44], ILM peeling is known to decrease retinal sensitivity [25, 45, 46]. No conclusion has been reached as to which cases should be treated with ILM peeling. Moreover, brilliant blue G, and indocyanine green, and triamcinolone acetonide are commonly used as visualization agents for membrane peeling [47–49], but they are used at the discretion of each physician, and no clear criteria exist for their use. Similarly, because no large-scale studies have been conducted, the choice of the gauge size of the vitrectomy system, the type of intraocular forceps, and the use of tamponade material (balanced salt solution, air [50, 51], and gas [52]) is at the discretion of each surgeon. In addition, various techniques have been reported for ERM cases associated with EPs, which are frequently seen in LMH, including EP removal [53, 54], EP embedding [55, 56], and ILM peeling without EP implantation [57]. However, there have been no large-scale studies on the postoperative outcomes of these techniques. Furthermore, postoperative complications of ERM include cataract progression [58], posterior capsular opacification [59, 60], epiretinal membrane recurrence [44], cystoid macular edema (CME) development [61], postoperative endophthalmitis [62, 63], retinal tears and detachment [64], and macular hole [65]. However, the incidence of each of these complications is low, and no analysis of large case series has been performed since the widespread use of MIVS, so the exact incidence and pre- and intraoperative factors associated with each complication are unknown. To address these important questions, we will employ statistical techniques like multivariate analysis and other modeling approaches, such as multilevel mixed models. In addition, statistical methods such as multilevel mixed models and quasi-comparative study designs with propensity scores and control variables will be used.

